## Background

Difficult airway management remains a cornerstone of clinical anesthesiology. Difficulty in tracheal intubation is the most common factor related to serious airway complications during general anesthesia [1]. Recently, the combination of the fiberoptic bronchoscope and the laryngoscope led to the development of video-laryngoscopes, providing a video-based view of the glottic opening, with or without additional guidance of the tube towards the tracheal opening. Six devices are under prominent focus in recent publications.

1) The Airtraq (Prodol Meditec SA, Vizcaya, Spain) was the first video intubation device that featured a channel guiding the tube towards the tracheal opening. The blade of the Airtraq is disposable. One study published in 2007 in *Anesthesiology* showed a 100% success rate at first attempt when using manual inline stabilization [2].

2) The A. P. Advance Video-laryngoscope (Venner Medical SA, Singapore) is based on a standard Macintosh laryngoscope that can be used as a stand-alone direct laryngoscope, or as a video-laryngoscope with a monitor attached to the handle and includes a “difficult airway” blade. A manikin study showed short intubation times for certified paramedics with the A.P. Advance [3], but large adequately powered, randomized controlled trials in difficult airway scenarios are lacking.

3) The C-MAC (Karl Storz, Tuttlingen, Germany) features size 2, 3 or 4 Macintosh blades or a “D”-blade (Difficult Airway Blade). The D-blade failed at first attempt in 30% of patients who showed a Cormack-Lehane grade 3 or 4 in a study by the inventor of the design [4]. One study shows a 93% success rate with the C-MAC using size 3 and 4 blades, compared to 84% for direct laryngoscopy when using manual inline stabilization, but intubation took longer [5].

4) The GlideScope (Verathon Inc., Bothell, WA, USA) is a widely used non-guided video-laryngoscope consisting of a curved video blade (single-use or reusable) and a special stylet to be used with the tracheal tube. An observational study in 50 patients showed a 100% success rate of the GlideScope in a difficult airway model using stiff extrication collars [6]. It also reduced intubation times compared with the conventional Macintosh laryngoscope in patients under manual inline stabilization [7].

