### Sample size calculation

Most previous studies have based sample size calculations on differences of the intubation difficulty score (IDS), developed by Adnet in 1997 for direct laryngoscopy [12]. However, a retrospective study by McElwain has raised concerns about the validity of the IDS with VLS [13]. The most important outcome parameter for VLS or any guided intubation devices is the success rate. Most available data are from patients with normal airway anatomy and, therefore, not comparable with our setting. Only one study immobilized the patients’ necks with collars to investigate the C-MAC in 43 patients. That study found an overall success rate of 88% [10]. This is an unacceptable low success rate for the management of a difficult airway, but the study was underpowered: we calculated the 95% CI in that study to be 0.75 to 0.95 for overall success rate.

In order to rate an intubation device as “successful”, we define that the lower limit of the 95% CI should not be smaller than 0.9. We based our sample size on these values, congruent with our findings in a small pilot sample. We calculated the necessary sample size to obtain a distance of 0.05 to the expected success rate of 0.95, provided a probability of 0.95 and a power of 80% (SAS v.9.1, SAS Institute Inc., Cary, NC, USA). A total of 107 patients per device are necessary for this lower limit of 0.9. A total of 642 (6 × 107) patients will be necessary based on these assumptions, which leads us to include 720 patients to compensate for dropouts or missing data.

Secondary endpoints include parametric data, such as time necessary until success. Time until success has varied widely among different devices in published studies. Furthermore, that parameter seems to be influenced by the anesthesia provider. Therefore, we based our sample size calculation on first attempt success rate.

Because available data about our primary outcome, the first attempt success rate in a simulated difficult airway scenario, are scarce, we will recalculate sample size after the first 120 patients, based upon the values obtained from the first 20 patients for each device. In order to reduce bias, all participating investigators will remain unaware of results obtained from these 120 patients.

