### Statistical analysis

For the primary outcome, it will be analyzed for each laryngoscope whether the 95% confidence interval of its primary success is below 0.9. For the secondary outcome parameters, the data distribution will determine which statistical test will be used. For frequencies (for example, number of required manipulations, overall attempt success, complications) chi-square test or Fisher’s exact test will be used. Parametric data will be analyzed using ANOVA; for non-parametric continuous data Kruskal-Wallis test will be used. For comparison between two devices, we will use Student’s *t*-test and Mann-Whitney’s *u*-test, as appropriate. We will do *a priori* comparisons of the time necessary until success between the unguided VLS and any of the guided VLS.

Data will be presented as mean with standard deviation, median and interquartile range, or number and percent. Effect sizes (with 95% CI) will be reported as Cohen’s d for interval data and as odds ratio for proportions. A probability of 0.05 is considered as statistically significant.

The patient flow diagram according CONSORT guidelines is provided in Figure 1.

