### Generalizability

In this clinical trial, we will use a statistical model that may be incorporated in future trials as well. Most clinical airway studies seek to prove a difference between devices, or postulate agreement within pre-defined values, some are designed as so called “non-inferiority” trails. In this study, we pre-define an important clinical value as a benchmark on which all devices studied are compared with the 90% minimal first attempt success rate. We believe an airway device should strive for this success rate, although that would still mean a failure in 1 out of 10. However, standard procedures in the difficult airway model used for this study have been shown to perform even less well: direct laryngoscopy succeeds only in 39.5% of cases [17] and rigid fiberoptics fail in 9 to 14% (own data, not published yet). Flexible fiberoptic intubation would be the method of choice, however, it is highly operator dependent and time consuming [18], and showed recently a not that impressive first attempt success rate of only 79% [19].

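### The odds ratio is the only effect measure named for proportions, but the trial's questions, above all the 10% injury margin, are on the absolute scale

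*Protocol article*

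**What the plan says.** In the protocol article, Statistical analysis:

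- Effect sizes carry a 95% CI and are Cohen's d for interval data "and as odds ratio for proportions". No other between-group measure for proportions is named.
- Description: "Data will be presented as mean with standard deviation, median and interquartile range, or number and percent".
- Tests for frequencies: "overall attempt success, complications) chi-square test or Fisher’s exact test will be used".
- Primary outcome: "it will be analyzed for each laryngoscope whether the 95% confidence interval of its primary success is below 0.9". No odds ratio enters here.

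Elsewhere the questions are put on the absolute scale. The Generalizability section says "we pre-define an important clinical value as a benchmark on which all devices studied are compared with the 90" percent minimum. The third hypothesis under the specific aims says that minor airway injury, guided against unguided, differs by no more than 10%; its null is a larger difference. The second group of hypotheses expects higher overall success with guided devices.

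**The concern.** The plan names a ratio where its hypotheses ask about differences. For hypothesis 3 this is more than a matter of taste. The margin is a fixed amount, a chi-square or Fisher test only tests equality, and an odds-ratio interval does not translate into percentage points without a base rate. As planned, no named analysis answers the question.

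A second, smaller issue is estimability. If one arm of a contrast has no failures or no events, the sample odds ratio is 0 or infinite, and the usual (Wald) interval does not exist. If both arms are empty, the odds ratio is undefined. This could arise for overall success or for rare harms. An ad hoc correction would then be needed to produce the promised CI.

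**Working it through.** **1. Does the sample size depend on the odds ratio?** The protocol states no figure for an odds ratio. Its 107 per device comes from the precision of one proportion, "to obtain a distance of 0.05 to the expected success rate of 0.95". The smallest n giving an 80% chance that the 95% CI half-width is at most 0.05, at a true rate of 0.95, is 104 (Wilson) or 109 (Agresti-Coull), which bracket 107. No odds ratio is involved.

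**2. Can an odds ratio decide a 10-point margin?** The protocol gives no injury rate, so a range of base rates is assumed. OR = [p2/(1−p2)] / [p1/(1−p1)] with p2 = p1 + 0.10:

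| p1 vs p2 | OR |
|---|---|
| 5% vs 15% | 3.35 |
| 10% vs 20% | 2.25 |
| 20% vs 30% | 1.71 |
| 30% vs 40% | 1.56 |

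Conversely, hold the odds ratio at 2.25. From a base of 5%, the odds are 0.0526 × 2.25 = 0.1184, a rate of 10.6%, so 5.6 points. From 30%, the odds are 0.4286 × 2.25 = 0.9643, a rate of 49.1%, so 19.1 points. The same odds ratio lies inside the margin in one case and outside it in the other.

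**3. Can a risk difference decide it at the planned size?** With 720/2 = 360 per class and equal true rates p, the approximate half-width is 1.96 × √(2p(1−p)/360): 3.2 points at 5%, 5.8 at 20% and 7.2 at 40%. All are below 10, so the planned size can support a verdict.

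**4. How often does a zero cell arise?** P(no failures among n) = p^n, and P(at least one of six devices) = 1 − (1 − p^n)^6, with n = 720/6 = 120 per device.

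| True success | One device, n = 120 | Any of six | One class, n = 360 |
|---|---|---|---|
| 0.93 | 0.02% | about 0.1% | about 0 |
| 0.95 (planned, first attempt) | 0.2% | 1.3% | about 0 |
| 0.98 (assumed) | 9% | 43% | 0.07% |
| 0.99 (assumed) | 30% | 88% | 2.7% |

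Overall success over two attempts is not given. If half of the 5% first-attempt failures are rescued, it is 0.95 + 0.5 × 0.05 = 0.975. If a second attempt succeeds independently at 0.95, it is 0.95 + 0.95 × 0.05 = 0.9975. P(no failures) on one device is then 5% to 74%.

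For a harm at an assumed 0.5%, P(no events) is 0.995^120 = 55% per device and 0.995^360 = 16% per class.

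**5. What does the odds ratio show?** 95% vs 90%: OR 19/9 = 2.11, failure risk ratio 10/5 = 2.00, success risk ratio 1.06, difference 5 points. 99% vs 97%: OR 3.06, failure risk ratio 3.00, success risk ratio 1.02, difference 2 points. At 107 per device, 95% vs 90% would give OR 2.11 (Wald 95% CI about 0.72 to 6.18) and a difference of 5 points (about −2.0 to +12.0).

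**The case against.** The strongest reply is that this is a reporting preference. Numbers and percentages will stand beside every odds ratio, Fisher's test is valid with empty cells, an exact conditional interval still has one finite bound, and zero-cell handling can be left to an analysis plan that is not shown. The primary conclusion is already on the absolute scale. Most of this stands and keeps the point minor. It does not cover hypothesis 3: percentages without an interval for their difference cannot judge a margin, and neither can a test of equality.

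Two stronger readings are tempting, and the documents do not support them.

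- *A reader might infer that the odds ratio will often be undefined for each device.* An odds ratio belongs to a contrast, not to a device. At the planned 0.95 an empty failure cell is very unlikely. The two 100% results in Background are weak support: for one, the Airtraq study, "showed a 100% success rate at first attempt when using manual inline stabilization", a setting the article itself separates from its collar model; the other is "An observational study in 50 patients showed a 100% success rate of the GlideScope in a difficult airway model". The article also cites 88% overall success for the C-MAC with collars and 93% with manual inline stabilization, rates at which empty cells practically do not occur. Nor are pairwise device contrasts of proportions clearly planned: the sentence on two-device comparisons names only tests for continuous data. The stated success contrast is guided against unguided, where an empty class is rare even at 0.99.
- *A reader might infer that the odds ratio exaggerates effects.* It stays close to the failure risk ratio (2.11 against 2.00), and it rightly says that failures double. Nor are 5 points trivial, since that is the distance on which the sample size rests. The fair statement is that it does not show the absolute difference.

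**Conclusion.** The point holds as a minor one. The only effect measure named for proportions is on a different scale from the trial's questions, and it cannot decide hypothesis 3. This rests on reading the 10% as percentage points, which the wording about differences of rates suggests but does not state.

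The zero-cell problem is conditional. It matters for device contrasts in overall success at about 0.98 or above, and for rare harms, both at assumed rates. It is not a concern for first-attempt success at 0.95. The primary analysis, the sample size and the data to be collected are unaffected.

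**What to change.** In Statistical analysis, name the difference in percentage points with a 95% CI valid at 0% and 100% (Newcombe or Miettinen-Nurminen) as the effect measure for proportions, above all for guided against unguided devices. State that hypothesis 3 is judged by whether that interval lies within ±10 percentage points, and confirm that percentage points are meant. Keep the odds ratio as a supplementary measure. The cost is a sentence or two of text, with no change to data collection or sample size.

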**Figure 1 F1:**
[figure not shown]
CONSORT flow diagram.

### Detailed study plan

#### Consent procedure

Patients will be recruited from the operating room schedule of the corresponding hospitals. Written, informed consent will be obtained from each patient on the day before surgery. All participants will be given a copy of the *Patient Information Sheet* and be specifically informed that they may decline to participate in or withdraw from the study at any time.

#### Allocation of patients

Patients with written informed consent are randomly allocated to one of the six devices. The allocation sequence will be generated using online randomization software (http://randomization.com) in blocks of 30 intubations for the devices and stratified for each participating center and for each physician. The allocation will be concealed in sealed, opaque, sequentially numbered envelopes and will not be opened until the patient is anesthetized.

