**Methods/Design:**

The objective of this trial is to evaluate and to compare the clinical performance of three video-laryngoscopes with a guiding channel for intubation (Airtraq™, A. P. Advance™, King Vision™) and three video-laryngoscopes without an integrated tracheal tube guidance (C-MAC™, GlideScope™, McGrath™) in a simulated difficult airway situation in surgical patients. The working hypothesis is that each video-laryngoscope provides at least a 90% first intubation success rate (lower limit of the 95% confidence interval >0.9). It is a prospective, patient-blinded, multicenter, randomized controlled trial in 720 patients who are scheduled for elective surgery under general anesthesia, requiring tracheal intubation at one of the three participating hospitals. A difficult airway will be created using an extrication collar and taping the patients’ head on the operating table to substantially reduce mouth opening and to minimize neck movement. Tracheal intubation will be performed with the help of one of the six devices according to randomization. Insertion success, time necessary for intubation, Cormack-Lehane grade and percentage of glottic opening (POGO) score at laryngoscopy, optimization maneuvers required to aid tracheal intubation, adverse events and technical problems will be recorded. Primary outcome is intubation success at first attempt.

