## Methods/design

### Study design

The SWIVIT trial is a prospective, patient-blinded, multicenter, randomized controlled trial at the anesthesia departments of the University Hospital of Bern, the University Hospital of Lausanne and the University Hospital of Geneva, all in Switzerland.

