We will compare time to intubate in unguided vs. guided VLS as the secondary outcome. There are not sufficient data available to calculate sample size for this secondary outcome parameter. Therefore, we base our sample size calculation on effect size: based on an estimated medium effect size (Cohen’s d of 0.5; assuming normal distribution), 64 samples per group are necessary, given a 0.05 level (*P* = 0.05) and 80% power. Because our primary outcome requires 107 patients per group, we are well within the necessary sample size even for this secondary outcome parameter.

Experience with the device is expected to be a major confounding factor. Only a limited number of experienced anesthesiologists at each study center will perform the intubation. To avoid a learning curve bias and to minimize variation in the performance, only anesthesiologists who have intubated patients without any airway pathology several times with each device until they feel competent with the devices will participate. We did not set *a priori* a fixed figure of intubations for each device because the individual experience with different devices is very divergent between the study centers and the participating anesthesiologists. Ideally, experience with the device should be equal, and prior experience will be recorded. We limit participants per center to a maximum of four physicians.

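### A single stated block size of 30 within each physician's own sequence lets an operator who counts cases deduce a small share of late assignments (minor)

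*Protocol article*

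**What the plan says.** All references are to the protocol article.

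- **Allocation of patients.** "Patients with written informed consent are randomly allocated to one of the six devices", and the sequence is made "in blocks of 30 intubations for the devices and stratified for each participating center and for each physician". No other block size is given, no variation in size is described, and nothing says that the size is withheld from operators. Concealment is by numbered, opaque, sealed envelopes that stay closed until the patient is under anesthesia.
- **Study design.** "The SWIVIT trial is a prospective, patient-blinded, multicenter, randomized controlled trial". No blinding of the operator is described there or elsewhere.
- **Sample size calculation.** A small group of experienced anesthesiologists performs the intubations: "We limit participants per center to a maximum of four physicians". The need is 107 per device, 642 in all, and the planned total is raised to 720 as an allowance for losses.
- **Consent procedure.** "Patients will be recruited from the operating room schedule of the corresponding hospitals", with consent on the day before surgery.
- **Trial status.** Fewer than 10 patients had been enrolled when the article was submitted.

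**The concern.** Stratifying by physician means that the history needed to work out the next assignment is the operator's own list of cases. With one known block size, counting shows which devices are used up and, at the end of the block, which one remains. Sealing the envelopes and opening them late does not remove this, because the information comes from past assignments and not from the envelope.

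What is at stake is the independence of patient and device. Patients come from the operating room schedule, and each of up to four physicians at a center has a separate sequence. An operator who expects, or can exclude, a device therefore has some room to influence which patient, or which colleague, takes the next envelope. First-attempt success depends on operator and patient, and each device is judged against 0.90, so selection of this kind is worth closing off where that costs little.

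**Working it through.** The article states no predictability figure, so there is none to reproduce.

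**Inputs**
- Block size 30 and six devices (Allocation of patients). Equal allocation is inferred from 6 × 107 (Sample size calculation), which gives 30/6 = 5 assignments per device per block.
- 720 patients: 720/30 = 24 blocks if all are completed.
- Three hospitals (Abstract) with at most four physicians each: at most 12 sequences, so on average at least 720/12 = 60 patients, or two blocks, per physician.
- Inferred, not stated: the operator knows each device used, performs all intubations in his or her own sequence, and keeps count.

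**Certain assignments (exact).** The assignment with *j* left in the block is certain when the last *j* are all one device:

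P(j) = 6 × C(30−j, 5−j) / C(30, 5), with C(30, 5) = 142,506.

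| Position | j | P(certain) |
|---|---|---|
| 30th | 1 | 6 × 23,751 / 142,506 = 1.000 |
| 29th | 2 | 6 × 3,276 / 142,506 = 0.138 |
| 28th | 3 | 6 × 351 / 142,506 = 0.015 |
| 27th | 4 | 6 × 26 / 142,506 = 0.001 |
| 26th | 5 | 6 × 1 / 142,506 = 0.00004 |

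The sum is 1.154 per block: 1.154/30 = 3.8%, and 24 × 1.154 = 27.7, about 28 of 720. That is a ceiling, since unequal caseloads leave blocks unfinished.

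**Ruled-out devices and best guess (simulation, 200,000 blocks).** The best guess is the device with most assignments left.

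| Position | Best guess correct | At least one device ruled out |
|---|---|---|
| 1st | 16.7% | 0% |
| 10th | 22% | 0.5% |
| 20th | 30% | 44% |
| 24th | 35% | 91% |
| 26th | 40% | 100% |
| 28th | 47% | 100% |
| 29th | 57% | 100% |
| 30th | 100% | 100% |

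From the 26th on a device is always excluded, because at most five assignments remain for six devices. Over the block, 9.07 of 30 guesses are right (30%) against 5 of 30 by chance (16.7%). At least one device is ruled out for about 35% of assignments.

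**Guided or unguided class only.** For two groups of 15, expected correct guesses are 15 + (2^30 / C(30, 15) − 1)/2 = 15 + (6.922 − 1)/2 = 17.96 of 30, or 59.9% against 50% by chance.

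**Alternative schemes.** The varying-size rows use sequences of 60 per operator and an operator who knows the set of sizes and guesses optimally.

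| Scheme | Certain | Device ruled out | Best guess correct | Class correct |
|---|---|---|---|---|
| Fixed 30 | 3.8% | 35% | 30% | 60% |
| Random 24, 30, 36, 42, 48 | 0.3-0.4% | 3-4% | 27% | 58% |
| Random 6, 12, 18 | 2.4-2.5% | 21% | 35% | 63% |

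Small random blocks make certainty rarer than fixed 30 does, but they raise best-guess accuracy. Fixed blocks of 6, 12 or 18 would be worse than 30: 41%, 36% and 33% correct overall.

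**The case against.** The strongest reply is that the plan is already fairly well protected. Thirty is five times the number of arms and less predictable than smaller fixed blocks. Envelopes are opaque, numbered and opened late. Consent is taken the day before, and patients with known or presumed difficult airways are excluded. Stratifying by physician answers a confounder that the article itself names. Nothing says that operators choose their cases, and a running tally of 30 is an assumption. Most of this stands, and it is why the point is minor. None of it removes the deduction by counting.

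A second reply is that the change does little for guessing as such: 30% to 27% for the device, 60% to 58% for the class. That also stands. What the change nearly removes is certainty and exclusion.

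Four stronger readings are tempting and not supported:

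- *Late assignments are generally predictable.* Only the 30th always is. Best guesses at the 26th to 29th are right 40% to 57% of the time, so they are often wrong.
- *The guided versus unguided comparison is biased by about 2 points.* That figure needs an assumed shift of plus or minus 5 points in success, acted on in every patient: 2 × 5 × (2 × 0.60 − 1) = 2.0. The document gives no basis for the 5 points, and the same formula still gives 2 × 5 × (2 × 0.58 − 1) = 1.6 after the change.
- *A device's pass or fail result would change.* No effect on the primary outcome can be derived. On the same assumed 5 points, acting only on certain cases moves a device's rate by about 0.038 × 5 = 0.2 points.
- *Collar fitting or the judgement of mask ventilation is compromised by the block size.* The article does not say whether the envelope is opened before or after the collar is placed. If before, the device is known then whatever the block size.

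**Conclusion.** The point holds as a limited weakness in concealment, of minor severity. The single block size, the stratification by physician and the patient-only blinding are in the text. That the operator sees the device follows from inserting it. That each operator performs the whole of his or her own sequence and keeps count is assumed.

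On those premises at most about 28 of 720 assignments can be known in advance, and other late assignments can be guessed better than chance without being known. Whether anyone would act on this, and what bias would follow, cannot be derived from the document, and no misconduct is implied. The block size is a choice the article states, so this is not a detail left to an unseen analysis plan.

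**What to change.** For blocks not yet started, keep the stratification by center and physician and keep the sealed envelopes. Have a person who does not intubate generate each physician's sequence with randomly varying block sizes that are large multiples of six, for example 24, 30, 36, 42 or 48. Avoid small sets such as 6, 12 and 18. Do not disclose the new sizes to operators; report them at the end. The size of 30 is already in print, so withholding can only apply to the new lists.

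The cost is new lists, new envelopes and one amended sentence, with no extra patients. Device balance becomes slightly looser: with up to 12 unfinished last blocks, the SD of each device's total is about 3 (3.4 in the check) around 720/6 = 120, or about 3.4/√12 = 1 per device within one operator's 60 cases. The margin to the planned 107 is 13 patients, nearly four SDs, and in 3,000 simulated trials no device fell below 107.

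### The secondary device comparisons leave out the physician and centre strata used to randomise, so they are mildly conservative and less precise than the design allows

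*Protocol article*

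**What the plan says.** Under Allocation of patients, the protocol article allocates the six devices "in blocks of 30 intubations for the devices", "stratified for each participating center and for each physician". Under Sample size calculation it caps the operators: "We limit participants per center to a maximum of four physicians". With three centres there are at most 12 physician strata.

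The same section explains why the operator matters. On time until success it says: "Furthermore, that parameter seems to be influenced by the anesthesia provider". On operators generally it says: "Experience with the device is expected to be a major confounding factor".

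Under Statistical analysis, the primary outcome is handled one device at a time: "it will be analyzed for each laryngoscope whether the 95% confidence interval of its primary success is below 0.9". For frequencies, "chi-square test or Fisher’s exact test will be used". For continuous outcomes across devices, "Parametric data will be analyzed using ANOVA; for non-parametric continuous data Kruskal-Wallis test will be used". Two-device comparisons use a t-test or Mann-Whitney test, and time is compared between unguided and guided devices. No stratified test, physician or centre term, or mixed model is named.

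**The concern.** Stratifying by operator makes each operator use all devices in nearly equal numbers, so differences between operators cancel from the device contrast. An analysis that ignores operator still counts those differences as random noise. The standard error is then larger than the true sampling error of the contrast: intervals are too wide, tests reject too seldom, and part of what stratification bought is given away.

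At stake is the precision of the secondary comparisons, above all guided versus unguided time to intubation, for which the article itself expects a provider effect.

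**Working it through.** **Inputs from the article.** Two-sided 5% level; standardised difference d = 0.5 for time, with 64 per group for 80% power; 107 per device required and 720 enrolled, so 720 / 6 = 120 per device and 3 × 120 = 360 per class (guided or unguided); blocks of 30, so 5 per device per block if devices are equally represented; at most 3 × 4 = 12 physicians. With equal recruitment, each physician has 720 / 12 = 60 patients, or two full blocks, and 10 patients per device.

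**Assumption.** The physician share of the variance of time (ρ) is not given. I use 10% and 20%, with a wider range of 5% to 30% in the simulation. d is in units of the total standard deviation.

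**Reproducing the plan's figure.** n = 2(1.96 + 0.842)² / 0.5² = 62.8, so 63 by the normal approximation. The noncentral t gives 63.77, so 64 per group, as stated.

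**Effect of leaving physician out.** With devices balanced within physician, the true variance of a difference in means is 2(1 − ρ)/n, while the unstratified test uses 2/n. Hence:
- true alpha = 2[1 − Φ(1.96/√(1 − ρ))]
- interval width relative to correct = 1/√(1 − ρ)
- unstratified power = Φ[(d√(n/2) − 1.96)/√(1 − ρ)]
- stratified power = Φ[d√(n/2)/√(1 − ρ) − 1.96]

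*ρ = 0.10:* √0.90 = 0.949. Alpha = 2[1 − Φ(2.066)] = 0.039; relative width 1.054.

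*ρ = 0.20:* √0.80 = 0.894. Alpha = 2[1 − Φ(2.191)] = 0.028; relative width 1.118.

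For power, d√(n/2) is 0.5 × √53.5 = 3.657 at 107 per group, and 0.2 × √180 = 2.683 at 360 per class.

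| Setting | ρ | Unstratified power | Stratified power |
|---|---|---|---|
| d = 0.5, 107 per group | 0.10 | Φ(1.789) = 0.963 | Φ(1.895) = 0.971 |
| d = 0.5, 107 per group | 0.20 | Φ(1.897) = 0.971 | Φ(2.129) = 0.983 |
| d = 0.2, 360 per class | 0.10 | Φ(0.762) = 0.777 | Φ(0.868) = 0.807 |
| d = 0.2, 360 per class | 0.20 | Φ(0.809) = 0.791 | Φ(1.040) = 0.851 |

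The value d = 0.2 is mine, chosen to show a smaller difference that the pooled comparison could still detect. At d = 0.5 with 360 per class, power exceeds 0.999 either way.

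**Simulation check** (12 physicians, devices balanced within physician, 108 per group). The unstratified t-test rejects a true null at 0.047, 0.041, 0.029 and 0.022 for ρ = 0.05, 0.10, 0.20 and 0.30. The model with a physician term stays between 0.048 and 0.052.

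**Binary outcomes.** With a physician standard deviation of 1 on the logit scale (assumed), null rejection is 0.041 for chi-square and 0.051 for Cochran-Mantel-Haenszel. Power for 0.95 against 0.85 is 0.888 and 0.900. The effect is small.

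The rank tests were not computed; the same mechanism applies to them.

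**The case against.** **The article is condensed.** It lists test families and never says that strata are excluded; ANOVA can carry a physician factor, and a fuller document may add one. This stands in part, and it is why the point is put as a wording change. But the article does not defer the choice. It names its tests, and chi-square, Fisher, Kruskal-Wallis, t and Mann-Whitney have no stratum term as named.

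**The error is on the safe side and small.** This stands. Only secondary comparisons are affected, and at the protocol's own d with 107 per group the loss is about one power point.

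**A reader might infer that the primary interval is too narrow**, because about 120 intubations per device come from at most 12 operators. The document does not support that. The operators are a small group chosen for experience, not a random sample. Conditional on them, unequal success rates give a variance no larger than binomial, so the simple interval is if anything slightly conservative. Take 12 operators with 10 patients each, a mean rate of 0.90 and a pass at 115 or more of 120 (the Wilson or Clopper-Pearson threshold; the article names no interval method). The false-pass chance is then about 1.5% or 1.4% with fixed operators whose rates spread as for an intraclass correlation of 0.02 or 0.05, against 1.6% under independence. Only if operators are treated as random does it rise, to about 2.4% and 3.6% at those correlations. That is a caveat on generalising beyond these operators. Nor is there any between-device contrast in the primary analysis in which the balance could be used.

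**A reader might also infer that recorded experience must be a covariate.** It need not be. Experience differs by device as well as by operator, so adjusting for it can change what is being compared. The article already deals with it by restricting who may intubate and by recording prior use.

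**Conclusion.** The mismatch between stratified allocation and the tests named for the secondary comparisons is real and worth correcting. Its consequence is lost precision, of modest size: the alpha and interval effects computed above hold for a physician variance share of 10% to 20% and near-complete balance within physician. If that share is 5%, almost nothing is lost (alpha 0.047); at 30% the loss is larger (alpha 0.022). Incomplete final blocks would weaken the balance somewhat. The finding does not reach the primary per-device analysis.

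**What to change.** State under Statistical analysis that the secondary between-device and guided-versus-unguided comparisons are analysed by the randomisation strata:
- **Time:** a linear model with physician as a factor or random intercept. Physicians are nested in centres, so a physician factor already absorbs centre.
- **Rank-based analysis:** the van Elteren test, stratified by physician.
- **Proportions:** Cochran-Mantel-Haenszel or logistic regression stratified by physician.

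Keep the primary per-device interval as planned. If wanted, add one sentence that the rates describe the participating operators.

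The cost is analysis wording and a little programming. Physician is known from the allocation, so there is no new data collection and no change to sample size or conduct. Trial status reports fewer than 10 patients enrolled at submission, so the change could be fixed before results are known.
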